## Abstract

**Abstract:**

**Introduction:**

Mental health at the workplace has been identified as a major priority by the World Health Organization (WHO). Despite its significance, international studies examining the influence of digital mental health interventions on workplace implementation and outcomes are lacking. The European Platform to Promote Well-being and Health in the Workplace (EMPOWER) platform is an eHealth intervention consisting of a website and web-based app designed to guide employers and employees on the prevention of common health problems, reduce presenteeism and absenteeism in the workplace. The aim of this paper is to describe the rationale and methods that will be used to conduct a maxi impact analysis of the processes undertaken to develop and implement the EMPOWER platform in European workplaces using the Global Impact Analytics Framework (GIAF) methodology.

**Methods and analysis:**

We will undertake a mixed-methods analysis of the impact of the process of implementation in the two phases of implementation (initiation and maturity—the early implementation phase). The primary methodology that will be used for the analysis is the GIAF and toolkit. The GIAF toolkit includes a taxonomy (knowledge map), glossary and checklists to examine and rate the EMPOWER project across various domains of impact: planning, pre-engagement, readiness, usability, dissemination, adoption and uptake. Information will be collected from a range of sources through different methods and used to rate the EMPOWER platform (website and app) on each domain. For reliability and validity, four raters will independently rate the EMPOWER platform using the same information. The analysis will include qualitative and quantitative methods to rate on standardised ladders and scales in the GIAF toolkit. Analysis will include descriptive statistics and non-parametric tests where relevant. The information gained will be reviewed in a subgroup (per country) and group (three country) analysis for formative and key summative learnings. These key learnings will be synthesised to generate organisational learnings and insights for the EMPOWER consortium to improve future intervention implementation processes.

**Ethics and dissemination:**

The impact analysis study protocol has been approved by the Research Ethics Committees of the University of Canberra (ID:202311841) and also the Fundació Sant Joan de Déu (PIC-39-20). The participating countries for the RCT (EMPOWER study) also obtained ethical approval through their respective ethical organisations in the participating countries. The impact analysis is registered with the Open Science Framework ID osf.io/eysc9. The EMPOWER project trial is registered at ClinicalTrial.gov with trial ID NCT04907604. The outcomes of the impact analysis study will be disseminated via conference presentations, peer-reviewed journals and key organisational learnings presented in relevant forums.

**Trial registration number:**

NCT04907604.

STRENGTHS AND LIMITATIONS OF THIS STUDYA limitation of the study is the limited opportunities to inform and educate consortium partners on the Global Impact Analytics Framework (GIAF) ecosystem approach to impact analysis.A further limitation of this study is the inherent complexity and need to rely on third-party data collection of dissemination activities in the study sites (workplaces) in real time.A strength of this study is the use of the GIAF which accommodates an International multiproject maxi impact assessment.A further strength is the GIAF framework, which provides a methodology for a rigorous evaluation, which focuses on the pathways to develop the European Platform to Promote Well-being and Health in the Workplace platform and then the process of its implementation in real-world workplaces.

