### Implementation sites and target audience

The EMPOWER platform will be implemented in small-medium enterprises and public companies from a variety of sectors in three cities and regions in Europe: Barcelona (Catalonia, Spain), Turku (Finland), Lodz (Poland). Three European countries were selected to represent different European welfare and health service models: Finland (represents the Scandinavian model), Spain (Mediterranean model), Poland (Eastern European model). Two target audiences will be considered: (1) the employees from the participating companies (primary target of the EMPOWER project) and (2) the employers of these companies (secondary target).

All employees from the selected companies meeting the criteria will be invited to participate in the cluster RCT. The inclusion criteria for participants are: (1) being aged 18 years or older; (2) having a mobile phone with Internet access; (3) having sufficient knowledge of the local language and (4) giving informed consent. Once these criteria are met, participants will be invited to download and use the app. After obtaining informed consent, employees will be asked to complete several questionnaires and will then be guided through different modules and content sections of the EMPOWER app.^22^ All employee participants will answer a total of three assessments via survey through the EMPOWER app. This allows for separate analyses at the country and company levels and the level of the EMPOWER cluster RCT.

Companies will be selected based on being a SME or public agency (<250 employees). The country coordinators will approach companies who meet the inclusion criteria, provide information about the study and the EMPOWER platform and invite them to participate. Those who consent will enter into a contract between the researchers and employers to affirm ethical considerations, data collection and communications. Each workplace (and thus the employees) will be randomised into the RCT.

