### Training and preparation for data collection

The preparation for the data collection commenced prior to finalisation of the EMPOWER app development and commencement of the RCT. The country coordinators are researchers from universities in each country and members of the EMPOWER consortium. They are located in each country (Finland, Poland and Spain) and have attended training. Their tasks include monitoring and managing the trial fieldwork in their country, data entry and validation, solving problems during the fieldwork and will remain in constant communication with other EMPOWER consortium partners. For the impact analysis data collection, there were three orientation/training sessions with the country coordinators. In October 2021, an introduction to the impact analysis and explanation of the GIAF framework was conducted online for country coordinators and included an orientation on the dissemination run sheet (a spreadsheet with predetermined categories), used to collect data for the dissemination domain (maturity phase). The run-sheet enables concurrent collection (rather than retrospectively) of the parameters of dissemination activities (eg, the communication frequency with an employer). Country coordinators enter data on the activities to recruit organisations/workplaces and to make the EMPOWER platform known and make it used. An additional training session was held in April 2022 with regards to the dissemination run sheet, and a third meeting in September 2022 on the usability and adoption questionnaires to be used at the end of the recruitment period. The usability and adoption questionnaires (for employers) are conducted through a semistructured interview with the employer representatives. In preparation for the data collection on the usability, the questionnaire was first refined to the three country contexts in English. Each country coordinator translated the questions into their country language (all being fluent speakers of the language). There was subsequent collaboration with each of the country coordinators to culturally adapt the questions, yet ensure they remained within the integrity of the intent of the questions. Finally, each country coordinator translated the usability questions into the relevant language. Support to understand and use the GIAF tools to collect information relevant for the dissemination, usability and adoption domains will be provided to country coordinators as needed.

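### Employees reach the app only by consenting to a cluster RCT, so country differences in uptake mix willingness to join research with acceptance of the platform, and the article does not list this as a limitation

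*Protocol article*

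**What the plan says.** **Route to the app** (Implementation sites and target audience). Companies that agree sign a contract with the researchers, and "Each workplace (and thus the employees) will be randomised into the RCT". For employees, "All employees from the selected companies meeting the criteria will be invited to participate in the cluster RCT". Informed consent is the fourth inclusion criterion, and then "Once these criteria are met, participants will be invited to download and use the app". After consent, "employees will be asked to complete several questionnaires and will then be guided through different modules".

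**Uptake** (Analysis). The calculation uses two counts, employees and EMPOWER users, by company or country. The result is mapped to a checklist and scored. Numbers invited and numbers consenting do not enter.

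**Use of the ratings.** The second research question asks whether the framework supports a comparison across the three countries. Unit of analysis plans country-level subgroup analysis in the maturity phase. Analysis sets uptake beside usability scores and adoption responses, and suggests that perceived usefulness may raise adoption and uptake.

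**Dissemination log** (Training and preparation for data collection). "Country coordinators enter data on the activities to recruit organisations/workplaces and to make the EMPOWER platform known and make it used". The same coordinators run the trial locally: "Their tasks include monitoring and managing the trial fieldwork in their country, data entry and validation".

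**Claim and limitations.** The strengths list refers to "the process of its implementation in real-world workplaces". The two listed limitations concern limited opportunity to educate partners about the framework, and reliance on third parties for dissemination data. The Discussion hopes that results may inform similar platforms elsewhere.

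**The concern.** Uptake is meant to show how far the target audience took up the platform. As calculated, it is the product of two decisions: to join a trial, and to use the app once in. The first can differ between countries for reasons unrelated to the app, such as attitudes to research, data protection worries or the way consent is explained. A country with low trial consent would then be rated as one where the platform was poorly taken up.

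Two planned readings are exposed. One is the country comparison of uptake. The other is the comparison of uptake with usability and adoption: usability is asked only of people who used the app and so had already consented, whereas the uptake denominator includes everyone who declined. High usability with low uptake could look like a paradox about the platform when it reflects refusal of the trial. Lessons for a later roll-out, which would not need trial consent, would inherit the problem.

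**Working it through.** The article gives no consent rate, usage rate or uptake figure, so there is nothing to reproduce. The check follows the text and then illustrates the mechanism on assumed rates.

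**Step 1: what uptake contains.** I read uptake as users divided by employees. (The Analysis section words the division the other way round; that is a separate point.) Since use requires consent,

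uptake = users / employees = (consenters / employees) × (users / consenters) = c × u.

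Here c is trial consent among all employees and u is app use among consenters. Only the product is planned for calculation. Employees who do not meet the inclusion criteria also stay in the denominator, so c absorbs ineligibility too.

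**Step 2: illustration.** Assumptions: u is the same in two countries, c is 20% in one and 40% in the other, and all counted workplaces have access to the app (the article does not say what control workplaces receive).

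| Use among consenters (u) | Uptake at c = 20% | Uptake at c = 40% | Gap |
|---|---|---|---|
| 40% | 0.20 × 0.40 = 8% | 0.40 × 0.40 = 16% | 8 points |
| 60% | 0.20 × 0.60 = 12% | 0.40 × 0.60 = 24% | 12 points |
| 80% | 0.20 × 0.80 = 16% | 0.40 × 0.80 = 32% | 16 points |

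In every row the ratio is two, which is the ratio of the consent rates. Use among consenters is identical.

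**Step 3: a milder case.** Suppose 40% of employees in each country would use the app if it were simply offered, and trial entry is accepted by 60% of them in one country and 80% in the other. Uptake is 0.40 × 0.60 = 24% against 0.40 × 0.80 = 32%, a gap of 8 points. If 30% or 50% would use it, the gap is 0.30 × 0.20 = 6 points or 0.50 × 0.20 = 10 points.

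**Step 4: would the planned analyses reveal it?** Coordinator interviews and the realist evaluation give qualitative context for high or low ratings. They may mention refusals, but they do not yield c and u separately. No other planned analysis in the article does so.

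**The case against.** The strongest reply is that the trial setting is stated openly and that several stronger readings go beyond the text. Most of this stands.

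- **A reader might infer that the real-world wording is false.** It is not. The sites are ordinary small and medium-sized companies and public agencies, and the phrase describes the setting. What is missing is a statement that access ran through a trial.
- **A reader might count the questionnaires as pure research burden.** The description of the app lists screening as its first component, and assessments run through the app. Some of that burden may be the product itself. The point therefore rests on consent, not on the questionnaires.
- **A reader might infer that nothing in the log separates trial steps from platform steps.** The run sheet has predetermined categories and definitions that the article does not show. They may already allow a split, although the text plans none.
- **A reader might infer that more recruitment contacts raise the dissemination rating.** Nothing in the article says so. Dissemination is rated on a ladder of qualitative levels, and contact frequency is only an example of what is logged.
- **A company approach can be both things.** Coordinators give information on the study and the platform together, and employers are the secondary target audience. Dropping all such entries would discard genuine dissemination.
- **The rates are assumed.** This is correct. The uptake checklist's thresholds are not shown either, so an effect on a rating cannot be demonstrated.

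None of this changes two facts: consent is a condition of access, and employees who decline remain in the denominator. The funnel is also imperfect. People may decline consent because the app does not interest them, so the consent step is not purely about research. The funnel shows where a country gap arises, not why.

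**Conclusion.** The point holds for uptake in the maturity phase. As planned, country uptake cannot distinguish a workforce that rejected the platform from one that declined research, and the article does not list this among its limitations. The conclusion rests on consent being required for app access and on all employees forming the denominator; both are in the text. Its size is unknown. The illustrations, from 6 to 16 points, restate assumed differences in consent and are not estimates.

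The scope is limited. Usability is touched only through selection of consenting users. Initiation ratings are made at project level and do not enter a country comparison. A reader might extend the point to every maturity domain, but nothing shows that readiness, for example, depends on consenting participants. For dissemination, the text shows recruitment and promotion in one log but not that the rating is distorted. This is a cheap improvement to what the uptake comparison can conclude, not a flaw that invalidates the study.

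**What to change.** 1. **Uptake.** Report it by country as a funnel: employees, invited, consented, opened at least one module. Show module use among consenters beside the overall percentage, and base the cross-country reading, and the comparison with usability and adoption, on both. App usage and employee numbers are already planned data. I assume that invitation and consent counts can be taken from the trial's records.
2. **Limitation.** State that implementation was observed in workplaces taking part in a cluster RCT, with app access conditional on trial consent. Restrict the transfer to other settings in the Discussion accordingly.
3. **Dissemination log.** Tag each entry as trial recruitment, platform promotion or both; existing entries can be tagged afterwards. Report the rating with and without the pure trial-recruitment entries, and keep company approaches that served both purposes. If the existing categories already allow this split, use them.

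The cost is a little coding and tabulation time and a more modest claim. No trial procedure changes.

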## Introduction

 Mental health at the workplace has been identified as a major priority by the WHO.^1^ Despite its significance, international studies examining the impact of digital mental health interventions implemented in the workplace are limited, with the focus on tools implemented in healthcare organisations.^2^,^4^ Inadequate evaluation and documentation of the process of implementation make it challenging for those implementing new digital interventions to replicate positive results or overcome barriers encountered in similar contexts.^5 6^ This is due to a range of factors including: inherent challenges posed by the different designs and methods in digital health research from the methods developed to test real-world applications; the rapid cycle of innovation in the digital sector; the inadequate time frame of funding of research projects (typically 4 years) to assess implementation; its cross-disciplinarity and differences in reporting methods.^7 8^

Another relevant barrier to evaluation is the absence of an international consensus on the terminology and classification (taxonomy) in implementation sciences. As an example, ‘Reach’, ‘Effectiveness’, ‘Adaptation’, ‘Implementation’ and ‘Maintenance’ are the domains of one of the main frameworks used in impact analysis,^9^ but the definitions and use of these terms vary widely among the research groups working in implementation.^9^,^11^ Terminology is defined as ‘a set of designations belonging to one special language’.^12^ Its purpose is to eliminate ambiguity from scientific language by means of standardisation.^12 13^

Added to the lack of a common taxonomy and its nomenclature, there is a dearth of standardised tools for quantitative impact analysis of the process of implementation.^14^,^16^ Previous work on impact analysis conducted by our group identified existing gaps in the evaluation of the process of implementation.^17^ Filling this gap is critical to set up inferences linking the inputs (resources) (eg, capacity and other characteristics of the ‘sender’ and the ‘recipients’ of an application), to the final research outputs (results) by providing analysis tools that shed light on the process (throughputs) of implementation.^17 18^

The Global Impact Analytics Framework (GIAF) is a novel methodology for impact analysis developed by an Australian-based team in partnership with a consortium of international topic experts. The GIAF uses an ontoterminology approach by including a taxonomy of the process of implementation, an accompanying glossary of terms and a series of checklists to evaluate the different domains of the taxonomy. The methodology uses qualitative and quantitative analysis. Through the use of the GIAF, there is also the potential to identify gaps in the process of implementation, to support organisations, funders and researchers to learn from their experience and make improvements.^19 20^

The GIAF can be applied at different levels of impact assessment—a mini, standard or maxi impact assessment. Parry and Stevens describe the mini impact assessment as a ‘desk top exercise’, the standard with greater quantification of impacts and a maxi as an extensive collection of new data and quantification.^21^ The GIAF mini impact assessment involves rating a project across 1–3 GIAF domains (ladders), a standard involves use of checklists across four domains and a maxi impact assessment involves five or more domains.

While several domains and the relevant checklists of the GIAF have been used in previous projects within education settings, clinical guidelines, digital mental health and social and healthcare. The European Platform to Promote Well-being and Health in the Workplace (EMPOWER) is the first multicountry project that will involve a maxi impact analysis involving multiple domains to test the use of both the initiation and maturity phases of the GIAF model. This project is conducted by a consortium of 15 organisations across 9 countries (8 European countries and Australia). All consortium partners are listed in the author’s note at the end of this paper. This project aims to develop and implement an occupational e-Mental Health Intervention in the workplace involving a digital platform (webpage and app). The approach for effectiveness analysis is a cluster RCT in three countries (Finland, Poland and Spain). The project commenced in January 2020 and will finish in June 2024. The EMPOWER platform has been developed especially for small to medium-sized enterprises (SMEs) and public agencies. The UK joined the consortium as a fourth demonstration site but will not participate in the impact analysis. Further information is available in the study protocol of EMPOWER.^22^

Stakeholders and potential EMPOWER platform users (eg, employees, employers, work health and safety personnel) have been involved in the design and development phases of the EMPOWER platform.^22^ Stakeholders continue to be involved in other aspects of the research performed by different consortium partners involved in the EMPOWER platform, including identifying barriers and facilitators, and development of policy recommendations as part of this study.

There are four independent evaluations of the EMPOWER platform performed by different groups within the consortium. These are:

Evaluation of intervention effectiveness (outcomes for individuals who use the EMPOWER App). This study will be conducted by Parc Sanitari Sant Joan de Déu, Sant Boi de Llobregat, Spain.A realist evaluation of the facilitators and barriers perceived by employers and employees on the use of the EMPOWER platform. This study will be conducted by Erasmus University Rotterdam, Rotterdam, the Netherlands.A cost-effectiveness analysis of the EMPOWER platform. This study will be conducted by Erasmus University Rotterdam, Rotterdam, the Netherlands.An impact analysis of the processes to develop and implement the EMPOWER platform. This study will be conducted by the University of Canberra, Canberra, Australia.

The topic of this manuscript is study 4, the impact analysis.

### Objective and aims

The aim of this protocol paper is to describe the rationale and methods that will be used to conduct an impact analysis of the EMPOWER project using the GIAF methodology. The objective of the manuscript is to present the GIAF methodology and how it will be used in the impact analysis of the EMPOWER platform in three European countries (Finland, Poland and Spain).

### Research questions

The research questions for the study are as follows:

To what extent can the GIAF Framework domains measure the development (Initiation) and early implementation (Maturity) phases of the EMPOWER platform in each country?Can the GIAF Framework be used to conduct a comparative analysis of the implementation of the EMPOWER platform across three countries? To what extent is the GIAF framework useful for measuring implementation process domains in order to provide reliable and informative answers to these research questions?

